### Eligibility Criteria

The intervention will be performed among the general Dutch population and is aimed at delaying and/or slowing down cognitive aging. A recent study by Singh-Manoux et al showed that cognitive decline can be measured as early as 45 years of age [42]. For this reason, participants are eligible for analysis of the primary outcome if they are at least 40 years or older. The upper age limit is a more pragmatic one, since the intervention is aimed at the Dutch workforce and 67 is the official retirement age. Apart from this age criterion, a participant has to have sufficient comprehension of the Dutch language to understand the digital informed consent form (see Multimedia Appendix 1) and should have regular access to an Internet connection. Because the entire intervention takes place outside of the research facility, no strict control or enforcement is possible over other ineligibility criteria such as neurodegenerative disorders, medicine use, or psychiatric symptoms. Therefore, we decided not to use these and other possible exclusion criteria, which also increases overall external validity.

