Keeping participants engaged with eHealth intervention programs has been a major problem since the field originated [7,57,58]. Several adherence-enhancing strategies are in place with the BAM. First, we upload weekly news updates on the homepage regarding health behavior and brain aging from the largest Dutch news websites. Second, on the dashboard of the participant we will upload weekly blogs and healthy recipes so that the content, apart from user input, changes on a weekly basis. Blogs discuss current topics in research on anything BAM-related in an easy accessible form. Recipes use fresh and healthy products and provide participants with ideas to prepare a healthy meal. Third, a personalized email reminder system is built into the BAM that can be adjusted to the participants’ individual needs. In their personal profile space, a participant can choose to receive daily, weekly, biweekly, or monthly email reminders. These reminders give an overview of current active goals and will link the participant directly to this goal after logging in. Fourth, during the registration process new participants can opt in to receive BAM newsletters, which will be sent using the MailChimp engine. At any time, participants can opt in or opt out of the newsletter. Last, participants get a personal profile space with a quick and easy overview of their current lifestyle. They can make adaptations to their lifestyle, see the results of their goals, and can adjust their settings.

Considering the field setting for this intervention, it is difficult to control for concomitant care, or better yet if the BAM inspires participants to make use of other platforms to alter their health behavior in a positive way, this accomplishes the BAM’s goals. The BAM can and may function as a gateway to healthy behavior. Using the GSM and the yearly follow-up, the BAM can track changes over time even if participants actively use outside help that the BAM refers them to.

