### Sample Size

We aim for a group size of 200 to find a 15% reduction on the risk factors (power calculation based on alpha <.05; power of 0.8; two-tailed; n=166; ±20% dropout).

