#### Secondary Analyses

Total set goals and specific lifestyle area goals will be reported descriptively. The changes of lifestyle within the goal setting group will be reported in absolute difference at end of intervention. The dose-response association between goals and change of lifestyle will be analyzed by multivariable linear regression model, and potential confounders will be adjusted. The change in self-efficacy and self-control scores will be reported in absolute difference at the end of the intervention. The association between the use of BAM and increased feelings of self-efficacy or self-control will be analyzed by multivariate analysis.

Analysis will be performed per protocol. The dropout in this pragmatic field study is likely to be high but can be considered a separate outcome for the implementation and feasibility of these types of intervention. As such, it represents valuable data about the quasi-experimental study design.

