We chose a quasi-experimental design as it seems more appropriate for a field setting in which it is highly impractical to initiate a randomized controlled trial, and blinding participants to the type of eHealth intervention they are receiving is practically impossible [65]. Theoretically, it was preferable to use a step-wedge cluster-randomized controlled design, but this was not feasible with the current 2-year intervention period. Since recruitment of companies is not guaranteed, cluster randomizing from the start is also difficult, especially since organizations are not very likely to see the incentive of participating as a control group. There is also a pragmatic side to the choice of the population. There is substantial theoretical background to select participants aged 40 and older [42], since in this part of the working population cognitive decline can already be measured, and they are more likely to be triggered by a dementia prevention program. People under 40 are less likely to be triggered by cognitive decline or even dementia prevention, as it is a disease associated with old age and only in later years a relevant threat to their health. Nonetheless, the BAM will allow participants under 40 to subscribe. However, lifestyle advice will be tailored to age cohorts starting at age 40.

Last, the use of a multimodal lifestyle perspective is a strength, as it gives potential participants a more integral overview of lifestyle. Providing a more comprehensive lifestyle overview allows the participant to prioritize one type of change over another and take a holistic approach to their own lifestyle. Also, benefits from changing one behavior may transfer to improved outcomes on another behavior that would go unnoticed in single modal interventions. Since the BAM is an eHealth intervention, tailoring to the needs of the participant is cheap after initial development costs have been incurred. Targeting personally relevant lifestyle factors after providing a more general overview should improve program adherence because the participant becomes aware of why they are working on a certain risk factor. This is important as adherence is often the crucial factor in lifestyle improvement programs.

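### The target of 200 leaves 160, not the required 166, at the protocol's own 20% dropout, and that allowance is not reconciled with the high dropout expected elsewhere

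*Protocol article*

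**What the plan says.** The Sample Size section is one sentence. It sets a target of 200 "to find a 15% reduction on the risk factors" and gives the basis as an alpha of .05 with "power of 0.8; two-tailed; n=166; ±20% dropout". I read 166 as the number needed in the analysis and 200 as that number inflated for dropout.

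Other sections describe the dropout the authors expect, without a figure:

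- Secondary Analyses: "The dropout in this pragmatic field study is likely to be high". The same paragraph says that the analysis will be per protocol.
- Intervention: "Keeping participants engaged with eHealth intervention programs has been a major problem since the field originated".
- Data Collection Methods: early loss of participants is treated as a serious risk in eHealth, and is a reason for keeping the baseline assessment short.

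Participant Timeline places the primary analysis after the 730-day follow-up. Recruitment expects enrolment to take about 4 to 5 months but closes entry to no one afterwards. Study Design refers the reader to the trial register for the sample size calculation; that record is not available here.

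**The concern.** Two things do not fit. First, the three numbers in the Sample Size section are inconsistent: 200 less 20% is not 166. Second, a 20% allowance over two years is hard to square with a protocol that expects high dropout from a self-guided online programme. The second matters more. The first costs a handful of participants. The second bears on whether the two-year primary analysis has anything like the power claimed, and a reader of the Sample Size section alone would not see the question.

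**Working it through.** **Inputs (Sample Size section).** Two-sided alpha 0.05; power 0.80; required n = 166; dropout d about 0.20; target 200.

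**Reproducing the target.**

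- Multiplying: 166 × (1 + 0.20) = 199.2, rounded up to 200. This matches the stated target.
- Dividing: 166 / (1 − 0.20) = 207.5, rounded up to 208. This is the number that leaves 166 after a 20% loss.
- Check: 200 × 0.80 = 160, which is 6 short of 166.
- Loss that 200 can absorb: 1 − 166/200 = 0.17, or 17%.

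**Can 166 itself be checked?** No. The 15% reduction is not stated to be absolute or relative, and no standard deviation, baseline rate or test is given. Trial calculations for one-sample and two-sample proportions, with assumed baseline rates from 20% to 95%, gave anything from about 26 to over 1,000. I therefore take the article's word that 166 gives 80% power. What follows is conditional on that.

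**Power at a smaller n.** With the effect held at the value that gives 80% power at n = 166, the normal approximation is

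power(n) = Φ[(1.960 + 0.842) × √(n/166) − 1.960].

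For n = 160: √(160/166) = 0.982; 2.802 × 0.982 = 2.751; 2.751 − 1.960 = 0.791; Φ(0.791) = 0.785.

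Only the 20% row below uses the article's own dropout figure. The other rows are assumptions of this review, shown because the article does not quantify high dropout.

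| Loss at 24 months | Left from 200 | Power | Enrolment needed to keep 166 |
|---|---|---|---|
| 20% (article) | 160 | 78.5% | 208 |
| 30% (assumed) | 140 | 73% | 238 |
| 40% (assumed) | 120 | 66% | 277 |
| 50% (assumed) | 100 | 58% | 332 |
| 60% (assumed) | 80 | 49% | 415 |

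The last column is 166/(1 − d), rounded up.

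**The case against.** The best defence is that the slip is trivial and the target is not binding. The article puts a plus-minus sign before the 20%, so the figure is approximate, and 17% loss keeps exactly 166. At a full 20% the cost is 6 participants and about 1.5 percentage points of power. The 200 is an aim, and open enrolment means it may well be exceeded. All of this stands as far as the slip goes. It does not settle the second point: reading the allowance as 17% makes it smaller still and widens the gap to the expectation of high dropout. Open enrolment makes a larger sample possible but does not correct the target. Late entrants help only if they reach 730 days before the analysis, and the article expects publication in early 2016.

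Three stronger readings are tempting, and the article does not support them.

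- *The 80% power will not be delivered.* The article never says how large high dropout is, and enrolment may pass 200. What can be said is that the stated target does not secure the power.
- *The per-protocol rule removes everyone who drops out.* Per protocol is not defined. The Intervention and Data Collection Methods sections separate leaving the programme from missing follow-up: those who unsubscribe are asked whether they will still provide the annual measurements. Programme dropout and 24-month outcome loss may therefore differ.
- *Registrants under 40 use up places in the 200.* The Discussion does say "Nonetheless, the BAM will allow participants under 40 to subscribe". But Eligibility Criteria already states that "participants are eligible for analysis of the primary outcome if they are at least 40 years or older", and the Sample Size section does not say that younger registrants count. Its silence on age is not a contradiction.

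**Conclusion.** The point holds in two parts of unequal weight. The inflation is wrong as written: at 20% loss, 200 leaves 160, and 208 would be needed. Taken alone, this lowers power from 80% to about 78.5%, which would not change the design. The weightier part is that the 20% allowance is not reconciled with the article's own expectation of high dropout, so 80% power at the 24-month primary analysis is not secured by a target of 200.

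The size of the second part cannot be fixed from the article. It ranges from a loss of about 7 percentage points of power at an assumed 30% loss to about 22 points at an assumed 50%. All power figures assume that 166 truly gives 80%, that each participant without a 24-month measurement is lost to the analysis, and that enrolment stops at 200.

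**What to change.** 1. Correct the sentence using n/(1 − d). Either state that 208 enrolled gives 166 at 20% loss, or state that 200 enrolled leaves 160 at 20% loss, with about 78.5% power.
2. State the expected loss of 24-month outcome data, make it consistent with the Secondary Analyses and Data Collection Methods sections, and distinguish it from leaving the programme.
3. Report the power of 200 over an explicitly assumed range, for example 73% at 30% loss, 66% at 40% and 58% at 50%. Alternatively, give the enrolment that would keep 166 at those rates: 238, 277 and 332.

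The cost is one rewritten sentence, one added sentence and a short table. As entry is not closed, aiming for 208 or more needs no change of design. The price is that the stated power, or the stated target, becomes less favourable.

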### Recruitment

Different recruitment strategies will be implemented to reach the necessary sample size. First, we will recruit medium to large commercial or governmental organizations through their human resources department or company employed medical staff. The BAM can provide organizations with a concrete intervention program that can substantiate their health policy. Organizations will be recruited by direct inquiry through telephone calls, emails, and will be targeted during several symposia, workshops, and congresses where the BAM will be presented. Once an organization is recruited, the research team in collaboration with the human resources department will develop a tailored recruitment strategy that maximizes the use of existing communication channels within the organization. These organizations are expected to deliver approximately 50% of all study participants.

Next to organizational recruitment, the BAM will also recruit participants in the general Dutch population. A press release will be issued by the Radboudumc to reach mainstream media to generate national attention for the study. The BAM will be advertised at the website of a cooperative research consortium that draws national attention because researchers from four nationally spread out universities will promote this website. Also, we will present the BAM at national and international health care conferences. We estimate that approximately 50% of all study participants will result from this free recruitment strategy.

The enrollment period will take approximately 4-5 months. However, due to the nature of the grant no actual stop in participant influx will be enforced. Participants will be allowed to enter the study at any given time. We will monitor participant influx over time so we can keep estimating the relevance and need for an intervention such as the BAM. Unless individual organizations determine otherwise, no financial incentives will be offered to potential participants. If this occurs, this will be disclosed in future publications.

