### Study Design

For this study, we will use a quasi-experimental longitudinal pre-posttest design, with measurements at baseline and after 12 and 24 months. Only Dutch individuals within the Netherlands will be recruited. The intervention website is programmed in Dutch and as such will not be feasible for implementation outside the Netherlands. Since the Brain Aging Monitor is an eHealth intervention and the Netherlands has an Internet penetration of 94% of all households [41], there is no limit to its potential reach within the Dutch-speaking community. There are no regional restrictions that keep uptake of the intervention pinned to the region of the research institute. Since the entire intervention is based on self-management, contact with the research team is strictly limited to technical support. Considering the fact that the protocol relates to a pragmatic field study that will recruit both at an individual and organizational level, we cannot give an accurate estimate of the number of sites needed to obtain the necessary number of participants. For a sample size calculation, we refer to the description of sample size (Nederlands Trial Register: NTR4144).

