### Statistical Analyses

#### Intervention Effects

Primary analyses will be unadjusted. Depending on the distribution of continuous, categorical, and interval outcomes, an appropriate distribution and relevant statistical models will be used. These models will assess intervention effects at end-of-intervention (1-year and 2-year) as well as the difference between 1- and 2-year measurements. Baseline characteristics will be compared between groups using *t* tests for continuous variables and chi-square tests for categorical variables. Mann-Whitney tests will be used when baseline data are not normally distributed. If necessary, multivariate analysis, including multi-analysis of variance and multiple regression, will be performed to adjust potential confounders, including baseline demographic and behavioral characteristics. The covariates associated with outcomes or contributing to a significant part of variation of used multivariate models will be adjusted as potential confounders. The final model will include these covariates or remove those that do not affect estimates, if models show evidence of overfitting.

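### About half the sample is expected to come through employers, but neither n=166 nor any named effect model allows for organisation; standard errors for mean change are too small if changes correlate within employers

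*Protocol article*

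**What the plan says.** All references are to the protocol article.

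- **Recruitment** describes two routes. For employers: "These organizations are expected to deliver approximately 50% of all study participants". For the general public: "We estimate that approximately 50% of all study participants will result from this free recruitment strategy". The employer route is specific to each employer: "Once an organization is recruited, the research team in collaboration with the human resources department will develop a tailored recruitment strategy". On incentives: "Unless individual organizations determine otherwise, no financial incentives will be offered to potential participants". The default is therefore none.
- **Study Design** leaves the number of organisations open: "we cannot give an accurate estimate of the number of sites needed to obtain the necessary number of participants". It refers the reader to the trial register for the sample size description.
- **Sample Size** sets a target of 200 to detect a 15% fall in risk factors and gives this basis: "power calculation based on alpha <.05; power of 0.8; two-tailed; n=166; ±20% dropout".
- **Statistical Analyses, Intervention Effects** makes the primary analyses unadjusted and leaves the primary model to be chosen by the distribution of the outcome. The t, chi-square and Mann-Whitney tests are named there for comparing baseline characteristics. For confounders: "If necessary, multivariate analysis, including multi-analysis of variance and multiple regression, will be performed".
- **Secondary Analyses** names a multivariable linear regression for the dose-response question.
- **Discussion, Principal Considerations** says that a stepped-wedge design randomised by cluster would in theory have been preferable, and discusses randomising companies as clusters. The authors thus recognise organisations as clusters when they discuss design.

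No section on sample size or analysis mentions organisation, recruitment route, a random effect or robust standard errors.

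**The concern.** Employees of one organisation share a recruitment channel, a workplace and an employer health policy, and all of these can change over two years. Their changes in lifestyle or cognition may therefore resemble each other more than those of unrelated people. If so, 83 employees carry less information about mean change than 83 independent participants. A standard error that ignores this is too small, its interval covers less often than claimed, and the real power at n=166 is below 80%.

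For association slopes (number of goals against lifestyle change, lifestyle change against cognitive change) the effect is less predictable. If the exposure differs mainly between employers, the ordinary standard error tends to be too small. If it varies mainly within employers, the error can be negligible or can go the other way.

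An analysis plan could add an organisation term later. It could not restore power to a recruitment target that was set without an allowance, and it could not use an organisation code that was never stored.

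**Working it through.** **1. The plan's own figure.** n=166 cannot be derived uniquely, because the article gives no baseline level, standard deviation or test. For a one-sample mean change at two-sided alpha 0.05 and power 0.80, it corresponds to a standardised effect d = (1.960 + 0.842)/√166 = 0.217. The target of 200 matches 166 × 1.2 = 199.2. Dividing by the expected retention would give 166/0.8 = 207.5, so 208; that is a separate matter. No design effect appears among the stated inputs.

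**2. Inputs.**
- From the article: n=166, alpha 0.05 two-sided, power 0.80, about half the sample from organisations.
- Assumed, because the article gives neither: k = 2 to 20 organisations of equal size, and an ICC of change scores between 0.01 and 0.05.
- General-population recruits are treated as independent.

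**3. Formulas, for the overall mean change.**
- Participants per organisation: m = 83/k.
- Design effect: DEFF = 1 + 0.5 × (m − 1) × ICC.
- Ratio of true to naive standard error: √DEFF.
- Coverage of a naive 95% interval: 2Φ(1.96/√DEFF) − 1.
- Effective n: 166/DEFF.
- Power of a test that uses the correct standard error: Φ(0.217 × √(166/DEFF) − 1.96).
- n needed for 80% power: 166 × DEFF. This keeps m fixed, so the extra participants come with extra organisations.

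**4. Worked case: 5 organisations, ICC 0.02.**
- m = 83/5 = 16.6 and DEFF = 1 + 0.5 × 15.6 × 0.02 = 1.156.
- Standard error ratio √1.156 = 1.075; coverage 93.2%.
- Effective n = 166/1.156 = 143.6; power 74.1%.
- n needed = 166 × 1.156 = 191.9, so 192.

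**5. Range.**

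| Organisations | m | ICC | DEFF | SE ratio | Coverage | Power | n needed |
|---|---|---|---|---|---|---|---|
| any | – | 0 | 1.00 | 1.00 | 95% | 80% | 166 |
| 20 | 4.15 | 0.01 | 1.016 | 1.008 | 94.8% | 79.4% | 169 |
| 20 | 4.15 | 0.05 | 1.079 | 1.039 | 94.1% | 77.0% | 180 |
| 10 | 8.3 | 0.05 | 1.183 | 1.087 | 92.9% | 73.1% | 197 |
| 5 | 16.6 | 0.02 | 1.156 | 1.075 | 93.2% | 74.1% | 192 |
| 5 | 16.6 | 0.05 | 1.390 | 1.179 | 90.4% | 66.1% | 231 |
| 2 | 41.5 | 0.01 | 1.203 | 1.097 | 92.6% | 72.4% | 200 |
| 2 | 41.5 | 0.05 | 2.013 | 1.419 | 83.3% | 50.6% | 335 |

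These are large-sample figures and are optimistic for the cases with very few organisations. They apply to a mean change and do not carry over to regression slopes.

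**6. Part of the loss is recoverable.** A model that gives less weight to clustered observations has effective n = 83 + 83/(1 + (m − 1) × ICC). In the last row this is 83 + 83/3.025 = 110.4, against 82.5 for the simple mean.

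**The case against.** The strongest reply is that the article does not commit to an independence-based primary analysis. The primary model is open, and a mixed model, GEE or cluster-robust error would all fit the text. The t tests concern baseline comparisons, and the multivariate models apply only if necessary and serve confounder adjustment. The article condenses a fuller protocol, and the register entry for the sample size is not at hand. There is no control group, no cluster allocation and no group delivery. Outcomes are individual change scores, so stable differences in level between employers cancel.

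Much of this stands, and it rules out several stronger readings that a reader might infer:

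- **That the intervals are too narrow as a matter of fact.** No ICC or cluster size is given, and correlated change is plausible but not documented.
- **That the named t tests are the faulty outcome analysis.** They yield no interval for an intervention effect.
- **That employer incentives are a known source of clustering.** They are only possible, and any would be disclosed.
- **That recruitment route confounds the main result.** With one group and no comparison, route cannot confound a mean change. It could confound an association, and the article's general rule on covariates does not exclude it.
- **That clusters of, say, 50 give a still larger inflation.** With 83 employees that is 83/50 = 1.66 organisations, which is not a workable equal-cluster scenario.

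What the reply does not remove is that the stated basis for n=166 has no cluster allowance, that each effect model actually named ignores organisation in its standard form, and that the authors themselves discuss organisations as clusters.

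**Conclusion.** The point holds in conditional form. Organisation is absent from the stated sample size basis and from every effect model named, while about half the participants are expected to arrive through employers. If change scores correlate positively within employers, standard errors for mean change that ignore this are too small. Over the assumed range the understatement runs from negligible (true standard error 1% larger than the naive one) to material (42% larger), and power runs from about 79% down to 51%. The middle case costs about six percentage points of power (80% to 74%). For slopes, neither size nor direction can be stated from the article.

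The result depends on the assumed ICC, the assumed number and equal size of organisations, and the half-and-half split. The ethics section describes the programme as implemented largely in companies, so the clustered share could be higher. The change is cheap and worth making; this does not show that the planned analysis is invalid.

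**What to change.** - Record an organisation code for every participant at registration, with general-population recruits coded as singletons.
- Fit the outcome models with a random intercept for organisation, or use cluster-robust standard errors, in either case with a small-sample correction.
- Include recruitment route as a covariate in the association models only. Do not combine it with organisation fixed effects: organisation membership determines route, so the two are collinear.
- State in Sample Size that n=166 and 80% power assume no within-organisation correlation, and give a design-effect range such as the one above.

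**Cost.** One stored field and one model term. Intervals become wider, possibly materially if few organisations join, and in that case the between-organisation variance is itself poorly estimated. A random-intercept model also gives less weight to employees of large organisations, so its estimated mean change can shift towards the general-population recruits if the two routes change by different amounts. Reporting mean change by route alongside would show this.
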